#### Moderator analyses

Moderator analyses will be conducted including potential moderators as interaction with treatment condition as independent variable in the main effect analyses. Potential moderators to be examined include severity of baseline stress symptoms, socio-demographic variables (e.g. age, gender, education etc.), sleep disturbances, emotion regulation skills, worrying and psychological detachment.

#### Economic evaluation

We will perform an economic evaluation from a societal perspective that includes all relevant costs and outcomes. A cost-effectiveness analysis and a cost-utility analysis will be conducted. For cost-utility analyses, quality-adjusted life years (QUALYs) will be calculated. A non-parametric boot-strapping method with 95% confidence intervals in percentiles will be used to assess differences between the intervention and control group. We will compare the intervention and control groups in terms of incremental costs and incremental effects. Towards this end, we will calculate the incremental cost-effectiveness ratio (ICER). We will use bootstrapping (5,000 times) to test the robustness of the ICER and to quantify the uncertainty in the ratios. The results will be shown in a cost-effectiveness plane and in a cost-effective acceptability curve. Additionally, the robustness of the base-case findings will be tested with a multi-way sensitivity analysis.

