#### Other measurements

Other measurements include demographic variables (e.g., age, gender, occupation etc.), the Effort Reward Imbalance Questionnaire – Short Form (ERI-SF) [75], the hope of improvement subscale of the German Patient Questionnaire on Therapy Expectation and Evaluation (PATHEV) [76] (adapted to the online training context), the German version of the Client Satisfactory Questionnaire (CSQ-8) [77,78] (adapted to the online training context), and a German questionnaire on the negative effects of psychotherapy (Ladwig, I., Rief, W., & Nestoriuc, Y.: Hat Psychotherapie auch Nebenwirkungen? Entwicklung des Inventars zur Erfassung Negativer Effekte von Psychotherapie (INEP) [Does psychotherapy have side effects? Development of an Inventory of Negative Effects of Psychotherapy (INEP)], submitted); adapted to the online training context). Approximately 30 minutes will be required to complete all questionnaires. For an overview of all outcome measures, see Table 2.

**Table 2 T2:** Outcome measures

	**T0**	**T1**	**T2**	**T3**	**T4**
					
Perceived Stress Scale	✔	✔	✔	✔	✔
Center for Epidemiological Studies Depression Scale	-	✔	✔	✔	✔
Hospital Anxiety and Depression Scales – Anxiety	-	✔	✔	✔	✔
Maslach Burnout Inventory – Emotional Exhaustion	-	✔	✔	✔	✔
Emotion Regulation Skills Questionnaire – Comprehension/Acceptance/Self-Support	-	✔	✔	✔	✔
Emotion Regulation Skills Questionnaire – General Distress	-	✔	✔	✔	✔
Attitudes Toward Seeking Professional Psychological Help Scale	-	✔	✔	✔	✔
Utrecht Work Engagement Scale	-	✔	✔	✔	✔
Recovery Experience Questionnaire – Psychological Detachment	-	✔	✔	✔	✔
Insomnia Severity Index	-	✔	✔	✔	✔
Penn State Worry Questionnaire – Ultra Brief	-	✔	✔	✔	✔
Trimbos/iMTA Questionnaire for Costs associated with Psychiatric Illness	-	✔	-	✔	(✔)
Quality of Life (EuroQol, SF-12)	-	✔	-	✔	(✔)
Demographic Variables Questionnaire	✔	-	-	-	-
Effort Reward Imbalance Questionnaire – Short Form	-	✔	-	-	-
Patient Questionnaire on Therapy Expectation and Evaluation (Online-Training)	-	✔	-	-	-
Client Satisfactory Questionnaire	-	-	(✔)	-	-
Questionnaire on Negative Effects of Online Trainings	-	-	(✔)	(✔)	(✔)
Potential Dropout Reasons	-	-	(✔)	-	-

*T0* Screening, *T1* Baseline, *T2* 7 weeks, *T3* 6 months, *T4* 12 months.

Assessments: ✔ = intervention and control group, (✔) = intervention group only

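### The economic evaluation names no adjustment for baseline costs or baseline utility, although both are collected in both arms; adjusting within the bootstrap would gain precision, mainly for QALYs

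*Protocol article*

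**What the plan says.** The Economic evaluation section of the protocol article sets out the comparison in one paragraph:

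- Estimand: "We will compare the intervention and control groups in terms of incremental costs and incremental effects".
- Interval method: "A non-parametric boot-strapping method with 95% confidence intervals in percentiles will be used to assess differences between the intervention and control group".
- Utility outcome: "For cost-utility analyses, quality-adjusted life years (QUALYs) will be calculated". No formula is given, and the instrument that supplies the utilities is not named.
- Ratio: "We will use bootstrapping (5,000 times) to test the robustness of the ICER and to quantify the uncertainty in the ratios". The results are then to be displayed in a cost-effectiveness plane and an acceptability curve.
- Robustness: "the robustness of the base-case findings will be tested with a multi-way sensitivity analysis". Its content is not described.

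No regression model or covariate appears in this paragraph. Table 2 has a row for the "Trimbos/iMTA Questionnaire for Costs associated with Psychiatric Illness" (TiC-P) and one for quality of life (EuroQol and SF-12). Both are marked at T1 (baseline) and T3 (six months) in both arms, not at T2, and at T4 (12 months) in the intervention arm only. Under Cost measures, the cost recall period is three months, so the T1 cost record describes the time before randomization.

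**The concern.** The controlled comparison has one baseline and one follow-up value each for costs and for utility. The baseline values have no stated part in estimating the group differences.

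This matters most for QALYs. If they are built as the area under a line from baseline to six months, half of the weight falls on a pre-randomization utility that treatment cannot affect. That half adds noise and no signal. Any chance difference between the arms at baseline enters the incremental QALYs directly, and again through its correlation with the six-month value. Resampling participants reproduces this variability in the interval but does not remove it.

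QALY differences over six months are likely to be small, so the noise can be as large as the effect sought. The article hypothesizes that the training is cost-effective and presents the economic evaluation as an advantage of the study, so precision that the collected data could supply is worth having.

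**Working it through.** **Inputs from the protocol article.** N = 264 (Sample size), allocated 1:1 (Randomization), so 132 per arm. Costs and EuroQol at T1 and T3 in both arms (Table 2). 5,000 bootstrap replicates (Economic evaluation).

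**Assumptions, not in the documents.** QALY over half a year by two-point trapezoid, Q = 0.5 × (U0 + U1)/2 = 0.25(U0 + U1). Equal utility SD at both times. Baseline-to-follow-up correlation r = .3, .5 or .7. EQ-5D SD of .15 to .25 where absolute figures are shown. Complete follow-up; the ratios below do not depend on the number per arm.

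**The plan's own figure.** The economic section states no result that can be recomputed. The sample size behind the 132 per arm does reproduce: d = .35, 80% power and two-sided α = .05 give 129 per arm (258) by the normal formula and 130 per arm (260) by the t test. Power at 132 per arm is .81.

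**Step 1: chance imbalance at baseline.** SE of the baseline difference = SD × √(2/132) = 0.123 SD. A difference above 0.2 SD in either direction has probability about .10. For SD .15 to .25, 95% of chance differences lie within ±1.96 × 0.123 × SD = ±.036 to ±.060. Through U0 alone that is ±0.25 × (.036 to .060) = ±.009 to ±.015 QALY. Including the carry-over to U1, the factor is 0.25(1 + r), which at r = .5 gives ±.014 to ±.023 QALY. For comparison, a utility gain of .05 at six months contributes 0.25 × .05 = .0125 QALY.

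**Step 2: precision for QALYs.** In units of the utility variance:

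- unadjusted: 0.0625(2 + 2r)
- adjusted for U0: 0.0625(1 − r²)
- ratio, adjusted to unadjusted: (1 − r)/2

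| r | Variance ratio | Unadjusted SE (in SD) | Adjusted SE (in SD) | Unadjusted/adjusted width |
|---|---|---|---|---|
| .3 | 35% | .050 | .029 | 1.7 |
| .5 | 25% | .053 | .027 | 2.0 |
| .7 | 15% | .057 | .022 | 2.6 |

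A simulation with 4,000 replicates agreed: unadjusted SEs .050, .053, .056; adjusted SEs .029, .027, .022. The mean unadjusted difference was within .001 SD of zero, so the estimate is not biased over repeated randomization.

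In absolute terms at r = .5, the 95% half-width is 1.96 × .0533 × SD = .016 to .026 QALY unadjusted, and 1.96 × .0267 × SD = .008 to .013 adjusted, for SD .15 to .25.

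**Step 3: precision for costs.** Follow-up cost is not built from baseline cost, so only the usual covariate gain applies: adjusted/unadjusted SE = √(1 − r²) = .95, .87, .71. Unadjusted intervals are 5%, 15% and 40% wider at r = .3, .5, .7. At r = .1 the excess is 0.5%.

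**Step 4: the ratio.** As a single illustration, take an incremental QALY of .01 (SE .01) and an incremental cost of 300 (SE 300), independent and normal. Each is positive in 84.1% of replicates, so the quadrants hold .841² = 71%, .841 × .159 = 13% twice, and .159² = 2.5%. Ratios of equal value then come from opposite situations (dearer and better, or cheaper and worse), and ordering them for a percentile interval has no clear meaning. The SE of .01 lies within the unadjusted range at r = .5 (.0533 × .15 to .25 = .008 to .013). Nothing in the documents says the trial will land there.

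**The case against.** The strongest reply is that silence is being read as a decision. A reader might infer that the plan commits to comparing raw costs and QALYs. The text does not say so. An incremental cost or effect is a between-group difference, adjusted or not, and a bootstrap can be applied to regression-adjusted differences. A condensed article may leave covariates to a fuller plan. This stands as a limit: if such a plan already adjusts for baseline, the point falls away. But the paragraph does specify the method, and someone following it as printed would run a two-group bootstrap without covariates.

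A reader might also infer that baseline imbalance biases the result or invalidates the intervals. It does neither. Randomization makes the unadjusted difference unbiased, and a valid bootstrap interval already includes chance imbalance. The loss is in precision, and in how far the one realized estimate can be moved by chance at baseline.

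A third tempting reading is that the plan promises a percentile interval for the ICER. The percentile intervals are tied to group differences. For the ratio, the text speaks only of quantifying uncertainty, and it already plans the plane and the acceptability curve, which handle replicates in several quadrants. The ratio point is therefore minor and conditional.

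Finally, the sizes rest on correlations, SDs and a QALY formula that the documents do not give. They also concern QALYs and costs only; the effect measure of the cost-effectiveness analysis is not specified in that section.

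**Conclusion.** The point holds as an improvement to the analysis, not as an error that invalidates it. The described bootstrap names no baseline adjustment, while the variables needed are collected in both arms.

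For QALYs the gain would be substantial at every correlation examined, provided they are built from the two controlled time points with baseline included; a different construction would change the figures. For costs it is small to moderate, and negligible if pre-randomization costs predict later costs poorly. The handling of the ratio needs only a conditional sentence.

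**What to change.** State in the Economic evaluation section, or in the analysis plan, that:

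1. Each of the 5,000 bootstrap samples resamples whole participants, keeping each person's costs, utilities and baseline values together.
2. Within each sample, incremental QALYs are estimated with adjustment for baseline EQ-5D utility, and incremental costs with adjustment for baseline TiC-P costs (separate regressions or seemingly unrelated regressions).
3. The cost-effectiveness plane and acceptability curve are drawn from these adjusted replicates.
4. Percentile intervals are given for incremental cost and incremental effect, and optionally for net benefit.
5. If replicates fall in more than one quadrant, the uncertainty of the ICER is conveyed by the plane and curve, and no percentile interval is put on the ratio.

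The cost is a few sentences and a few lines of code. Assessments, sample size and participant burden do not change. The choice should be fixed before group comparisons are seen, so that adjustment cannot be chosen by its result.

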## Discussion

In this study, we will examine the efficacy and cost-effectiveness of a web-based stress-management training in highly stressed employees. We expect that the stress levels of participants in the intervention group will be significantly lower after the training and after six months compared to these measures from the control group. Furthermore, we expect this intervention to be cost-effective.

The intervention content of the stress training was developed with a clear theoretical background based on Lazarus’ transactional model of stress [35]. A recent study of a web-based intervention aimed at reducing stress provides psycho-educational information about problem- and emotion-focused coping in one out of 13 training sessions [15]. However, there are currently no web-based stress-management interventions that have used the combination of problem- and emotion-focused coping based on the definitions of Lazarus [35] as the main theoretical basis. In the research on stress, problem-oriented coping methods such as the problem-solving training have always been strongly emphasized. In addition, many interventions include cognitive restructuring as a treatment component. With this focus, emotions are only addressed indirectly as a sub-area of cognitions. Recently, deficits in emotion regulation skills as a treatment target have gained attention in the field of mental health [37,41]. Emotion regulation has been shown to be relevant in a broad range of mental disorders [41] including depression [37-39] and anxiety [40]. Only now, the targeting of emotions as an autonomous treatment component finds its way into stress-management training formats. A study in hypertensive employees found that a stress-management intervention consisting of positive emotion refocusing and emotional restructuring techniques can improve stress, depression, emotional health and systolic blood pressure [84]. Furthermore, an intervention designed to increase emotional competence has been found to result in decreased perceived stress and lower cortisol secretion in adulthood [85]. However, to the best of our knowledge, there is no web-based stress-management training available that has included emotion regulation as main treatment component. Thus, the web-based training proposed herein includes emotion regulation as an innovative and promising component in addition to the traditional, established component of problem solving.

The inclusion of an economic evaluation constitutes a strong advantage of this study. There are a limited number of economic evaluations of worksite mental health interventions available [28]. The afore-mentioned RCTs on web-based interventions for managing stress [13-16,18,21-24] have not included full economic evaluations.

A number of studies of web-based stress-management interventions have been undertaken; however, little is known about moderators of treatment outcome. It is essential to know for which people with which personal characteristics, which training is most effective under what circumstances in order to optimize training circumstances for each individual based on his or her personal characteristics. Therefore, we include a variety of measurements that are assumed to be related to stress, such as emotion regulation skills [86,87], sleep disturbances [6], psychological detachment or worrying [62,88,89].

### Strengths

A major strength of the current study is the robust randomized controlled trial design, which is the gold standard for clinical trials. Furthermore, this is the first study in Germany to examine the efficacy and cost-effectiveness of a web-based stress-management intervention. We also include a large number of participants in this study to ensure sufficient power.

### Limitations and future directions

One limitation of this study is that no objective measurement of stress (e.g., cortisol levels) will be included. Due to feasibility limitations, only self-report measurements will be examined. Although self-reports always carry the risk of introducing subjective biases, it has been suggested that replacing self-reports with stress-related physiological measurements is not promising [90]. However, the completion of self-reports can be complemented with other measurements to provide more reliable data [90].

Another limitation of the proposed study is the potential self-selection bias. Participants will be eligible to apply for the intervention if they experience work-related stress. One must assume that the individuals who participate in this study possess certain characteristics. Therefore, the results of the current trial will only be applicable to persons who select themselves for this stress-management training.

For future studies it is worthwhile to investigate how much support is needed within the training to achieve the optimal trade-off between treatment outcome and economical costs, i.e., to maximize treatment outcome and simultaneously maintain the lowest level of support possible. A meta-analysis showed that interventions without an eCoach can be effective; however, the effect sizes without an eCoach are much smaller than those of interventions with an eCoach [12]. The current training includes a personal feedback from an eCoach after each of the seven sessions. It would be interesting to examine the size of the treatment effects that result from the application of other, less intensive and more economical support concepts, such as feedback on demand.

In the current trial, we will examine the efficacy of a guided self-help training in comparison to a waitlist control group. This design is therefore not suited to draw any conclusions regarding the effectiveness of the training compared to a face-to-face training, as has been examined elsewhere [27]. In a systematic review and meta-analysis, guided self-help programs for depression and anxiety have been found to have effects similar to those of face-to-face therapies [91]; thus, an investigation of the efficacy of a face-to-face version of the training compared to the web-based training would be worthwhile.

## Conclusions

This study aims to evaluate the efficacy and cost-effectiveness of a newly developed stress-management training for employees. If successful, this training could be made available to a large number of employees because of the low threshold accessibility and potentially low costs.

### Ethical considerations

This study has been approved by the ethics committee of the Philipps University Marburg (registration number AZ-2012-43K).

## Abbreviations

RCT: Randomized controlled trial; PSS-10: Perceived stress scale; DRKS: Deutsches Register für Klinische Studien; TAU: Treatment as usual; ART: Affect regulation training; CES-D: Center for Epidemiological Studies Depression Scale; HADS: Hospital Anxiety and Depression Scales; MBI-GS-D: Maslach Burnout Inventory; ERSQ-27: Emotion regulation skills questionnaire; ERSQ-ES: Emotion regulation skills questionnaire - emotion specific version; ATSPPHS-SF: Attitudes toward seeking professional psychological help scale – short version; (UWES): Utrecht work engagement scale; REQ: Recovery experience questionnaire; ISI: Insomnia severity index; PSWQ-PW: Penn state worry questionnaire-past week; QUALYs: Quality-adjusted life years; EQ-5D: EuroQol; SF-12: Short form 12; TiC-P: Trimbos and institute of medical technology assessment cost questionnaire for psychiatry; ERI-SF: Effort reward imbalance questionnaire – short form; PATHEV: Patient questionnaire on therapy expectation and evaluation; CSQ-8: Client satisfactory questionnaire; CONSORT: the Consolidated standards of reporting trials; NNT: Number needed to treat; ICER: Incremental cost-effectiveness ratio
